##### Secondary mental health outcomes

Our secondary mental health outcomes are (1) self-rated anxiety, depression and psychological well-being and (2) self-rated emotional reactivity following a negative mental experience (eg, unpleasant thought, feeling or memory) as measured using ESM. These measures have been included to address research questions 2a and 2b.

##### Mental health symptoms

This study will explore the potential impact of decentering training on mental health outcomes at baseline, mid-intervention and post intervention. Previous findings suggest that decentering is negatively associated with anxiety and depression^14–16^ as well as feelings of anger in adolescents.^38 39^ We will therefore include measures of each of these difficulties. Anxiety symptoms will be assessed using the Revised Child Anxiety and Depression Scale-Short Version (RCADS-15).^40^ The RCADS-SV is a 15-item scale measuring the reported frequency of various symptoms of anxiety and low mood. Internal consistency has been reported as good (Cronbach’s α=0.7-.96), as were test–retest coefficients and convergent validity. Depression symptoms will be assessed using the CES-D.^41^ The CES-D is a 20-item inventory measuring depressive symptoms experienced in the past week. Internal consistency is good, with Cronbach’s α=0.85–0.90. Concurrent and construct validity have been demonstrated. Anger will be measured using the State-Trait Anger Expression Inventory-2 Child and Adolescent (STAXI-2),^42^ which is a 35-item self-report measuring anger expression and control in adolescents. The STAXI exhibits good reliability, with Cronbach’s alpha coefficients ranging from 0.81 to 0.93, with good convergent validity.

Two measures will also be included to estimate the impact of decentering training on psychosocial strengths/difficulties and general well-being. The Strengths and Difficulties Questionnaire (SDQ) is a screening tool with five subscales (Emotional Symptoms, Conduct Problems, Hyperactivity/Inattention, Peer Relationships and Prosocial Behaviour) as well as an impact supplement to estimate psychosocial functioning. This tool was included to capture behavioural symptoms such as conduct difficulties and hyperactivity. The SDQ exhibits strong internal consistency, moderate test–retest reliability and good concurrent validity. Psychological well-being will be measured using the Warwick-Edinburgh Mental Well-being Scale (WEMWBS).^43^ The WEMWBS is a 14-item measure of positive mental health including positive affect, functioning and interpersonal relationships. The WEMWBS shows high-internal consistency, and good convergent and construct validity. Measures will be administered at baseline, mid-intervention and post intervention.

##### ESM emotional reactivity

This study will examine if the lagged effect of the decentering from difficult thoughts, feelings or memories (time=*n*) on later affect (time=*n* + 1) changes across training. One ESM items will capture general affect: ‘Right now I feel…’, answered on a 11-point Likert scale ranging from −5=Very negative to +5=Very positive. Two separate ESM items will capture the self-initiated use of decentering skills in response to negative mental experiences (table 1). These are: ‘Since the last message, I was able to distance myself from [a] a negative feeling *or* [b] unpleasant things on my mind’. Additional ESM items will check for the occurrence of negative mental experiences. These include checks of (a) negative feelings by asking ‘I feel Nervous/Sad/Irritated/Stressed’ and (b) unpleasant cognitive events by asking ‘Since the last beep, I was upset by a thought or memory’. This will be scored on a 7-point Likert scale from 1=Not at all to 7=Very much.

One item will assess the occurrence of unpleasant thoughts: ‘since the last beep, I noticed an unpleasant thought or memory’. This will allow us to control for the presence of unpleasant cognitive events from which participants can decenter. If the participant’s response is anything other than not at all, they will then complete three items to the content of these thought (table 1, items 8–10). If the participant’s response is not at all, they will complete three unrelated ‘branching’ items (table 1, branch items 1–3). This means the same number of item will always be administered.

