### Current study objectives

The primary aim of the current study is to investigate if decentering can be improved during adolescence via an intensive decentering training programme. This will be investigated (1a) at a trait level by examining changes in self-reported experience of decentering (via a standard decentering inventory) and (1b) at a situational level by examining self-reported use of decentering skills in response to momentary psychological stressors (via ESM assessments). Here, repeated measures of participants’ negative emotional reactivity towards momentary inner experiences (eg, feelings, thoughts and memories) will be recorded across the duration of the intervention. A secondary aim is to explore potential mental health outcomes associated with reinforced decentering skills. This will be investigated (2a) at the symptom level by examining relative change in self-rated anxiety, depression and psychological well-being and (2b) at the situational level by recording emotional reactivity towards momentary psychological stressors using ESM. A final exploratory aim is to investigate some of the cognitive correlates of decentering and training. Thus, this study will answer the following research questions: (1a) Is decentering training during adolescence associated with increased decentering reports relative to an active control condition? (1b) Is decentering training during adolescence associated with increased decentering in response to negative mental events relative to an active control condition? (2a) What is the impact of decentering training on youth mental health relative to an active control condition? (2b) What is the impact of decentering training on emotional reactivity towards momentary negative mental events relative to an active control? (3) What are the cognitive correlates of decentering training during adolescence?

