##### ESM analysis

Only participants who completed at least 33% of the ESM questionnaires will be included in the analyses, in line with ESM guidelines.^50^ Statistical analyses will be performed using hierarchical linear models. These models are especially suited to deal with dependency inherent in the data due their hierarchical structure: ESM observations (level 1) nested within individuals (level 2). Potential confounders will be included in the model as covariates. First, a linear growth model will be estimated to assess the effect of condition (decentering training vs active control) on decentering skills over time (ie, the duration of the intervention). Second, time-lagged analyses will be performed to evaluate if higher self-rated decentering skills when confronted with a momentary psychological stressor (time=n) predict significantly lower negative affect ratings at a later time point (time=n+1). We will also control for momentary negative affect ratings (at time=n). Random intercepts and random slopes models will be estimated. In hierarchical linear models, the fixed effects reflect the overall association between a predictor and the outcome of interest, whereas the random effects reflect individual differences in this association.

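### Question 2b asks whether training changes emotional reactivity relative to control, but the planned experience-sampling (ESM) model estimates only the decentering-to-affect slope and names no condition term

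*Protocol article*

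**What the plan says.** All references are to the protocol article.

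- **Current study objectives**, question 2b: "What is the impact of decentering training on emotional reactivity towards momentary negative mental events relative to an active control". This is a between-arm question about the response to an event.
- **Secondary mental health outcomes** names the matching outcome: "self-rated emotional reactivity following a negative mental experience", measured by ESM.
- **ESM emotional reactivity** then states its target. It begins "This study will examine if the lagged effect of the decentering from difficult thoughts, feelings or memories" at time n, and asks whether that effect on affect at time n+1 changes over training. Affect is a single general item, "answered on a 11-point Likert scale ranging from −5=Very negative to +5=Very positive". Of the item on noticing an unpleasant thought or memory, it says: "This will allow us to control for the presence of unpleasant cognitive events from which participants can decenter".
- **ESM analysis** describes two models. The first is a growth model of decentering skills by condition, which serves question 1b. For the second, "time-lagged analyses will be performed to evaluate if higher self-rated decentering skills when confronted with a momentary psychological stressor" predict lower negative affect at the next time point, controlling for negative affect at time n. Condition is named in the first model and not in the second.

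**The concern.** The first two sections set a quantity: how much affect worsens after a negative mental event, compared between arms. The last two set a different one: how strongly a person's decentering rating predicts later affect. In the stated analysis the stressor items are occurrence checks and controls. None is the predictor whose coefficient is the outcome.

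The two quantities can part company. The section on ESM decentering items expects momentary decentering reports to rise in the training arm. If they rise and each unit helps as much as before, affect after stressors improves while the slope stays where it was.

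Two misreadings are then possible. A flat slope may be taken as no effect on reactivity. A significant slope in the pooled sample may be taken as a benefit of training, although it can be present when training does nothing.

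**Working it through.** **Plan's own figure.** There is none for this outcome. The Sample size section rests on the Experiences Questionnaire. Its total of 90 at f=0.3 reproduces (power 0.804), but it has no bearing on ESM reactivity.

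**The two quantities.** Let A be negative affect (higher is worse), S the stressor (0 or 1) and D decentering:

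A(n+1) = ρ·A(n) + S(n)·[β − γ·D(n)] + noise

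- Reactivity (question 2b): β − γ·mean(D).
- The plan's lagged slope at stressor moments: −γ.

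Reactivity depends on β, γ and the mean of D. The plan's slope depends on γ alone.

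**Assumed values.** ρ=0.3, β=1.3, γ=0.3 and mean D=1, so reactivity is 1.3 − 0.3×1 = 1.0. There are three ways to halve it by the end of training in the decentering arm:

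- (i) Stressor impact falls: β=0.8, so 0.8 − 0.3 = 0.5. Slope unchanged.
- (ii) More decentering: mean D rises by 0.5/0.3 = 1.67 to 2.67, so 1.3 − 0.3×2.67 = 0.5. Slope unchanged.
- (iii) Each unit works better: γ=0.8, so 1.3 − 0.8 = 0.5. Slope changes by −0.5.

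**Simulation.** The 57 per arm and four beeps a day come from the protocol. Assumed are 100 training beeps per person (4 × 5 weekdays × 5 weeks, all answered), a stressor at 40% of beeps, and the values above. There were 60 runs per scenario, with within-person models and clustered errors. The plan's slope was given the favourable treatment of a condition-by-time interaction, which the protocol does not state.

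| Scenario | Change in plan's slope, by arm | Runs significant | Change in reactivity, by arm | Runs significant |
|---|---|---|---|---|
| No effect | −0.03 | 3% | 0.00 | 2% |
| (i) Stressor impact falls | −0.01 | 8% | −0.52 | 95% |
| (ii) More decentering | 0.00 | 5% | −0.50 | 97% |
| (iii) Each unit works better | −0.48 | 100% | −0.50 | 95% |

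With 60 runs, the standard error of a 5% rate is √(0.05×0.95/60) = 2.8 percentage points, so 8% and 3% are both compatible with 5%.

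**Second set of assumptions.** This used 46 completers per arm (57×0.8 = 45.6), a stressor at 50% of beeps, a benefit of 0.2 affect points per distancing point in both arms, and training raising distancing by 1.5 points. On a scale where negative is worse, reactivity moves by 0.2×1.5 = 0.30, from −0.60 to −0.30. Over 400 runs the share significant was:

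- between-arm test of the lagged slope: 5.8%
- between-arm test of affect on stressor: 93.5%
- between-arm test of mean affect: 94%
- pooled lagged slope: 100%

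In a further 300 runs in which training did nothing, the pooled slope was again significant in 100%.

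**The case against.** **The outcome is worded correctly in one place.** This is true. The list of secondary outcomes names reactivity after a negative experience, and the lagged model is tied to stressor moments. The defect is a mismatch between sections, not a wrong outcome throughout. Restricting to stressor moments does not change what the slope measures.

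**This is a condensed article, and a fuller analysis plan may exist.** A missing condition term alone might be left to such a plan. But the article states the target, predictor, outcome and adjustment for this analysis, and these do not match question 2b.

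**A reader might infer that training which halves reactivity would be reported as no change.** The documents do not support that. The Intervention section speaks of developing decentering ability, which does not exclude more effective decentering. Asking whether the lagged effect changes over training treats that route as open. Under it the slope detects the halving, as in scenario (iii).

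**The simulated result is built in.** Largely so. Holding the slope equal in both arms guarantees about 5% rejection. The simulations illustrate a structural fact and do not estimate how likely a miss is.

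**The two ESM models together would be informative.** Also fair. In the second set of assumptions, with a between-person SD of 1.5 to 2.0 (assumed), a comparison of means has roughly 95–99% power for a 1.5-point rise in decentering. With a significant lagged slope, that would suggest benefit. It remains an indirect argument: the lagged slope is an observational within-person association, and neither model compares affect after stressors between arms.

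**Conclusion.** The point holds as a mismatch between the question and the analysis. Question 2b is a between-arm question about affect after a negative mental event, and no model described in the protocol answers it. The lagged slope answers a different, mechanistic question, and as written it does so without reference to condition.

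A real reduction in reactivity could be missed if training changes the amount of decentering or the direct impact of stressors. It would be picked up if training makes each unit of decentering more effective. That pattern follows from the algebra and does not depend on the assumed values. The detection rates do depend on the assumed effect sizes, stressor frequency and full response. The 33% completion threshold would admit people with about 33 of 100 training beeps, so real precision would be lower.

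A significant pooled slope would not show a training effect. No section claims that it would, but nothing in the text guards against that reading.

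The consequence is limited to a secondary, exploratory aim of a feasibility trial. The primary Experiences Questionnaire analysis is unaffected. The change should be made, and before unblinding.

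**What to change.** 1. Keep the lagged decentering-to-affect model. Add condition and condition-by-time terms to the decentering slope, and label it a mechanism analysis. State one affect measure for it: the outcomes section uses the bipolar general item, the analysis section negative affect ratings.
2. For question 2b, specify a hierarchical model of momentary affect (item 1), with affect at the previous beep as covariate, on the stressor rating (item 6). The test is the stressor × condition × phase interaction, with phase being ESM baseline versus training. Item 6 covers the interval since the last beep and item 1 the present moment, so the order is right. Item 7 asks about being upset and already contains the reaction, so it suits the predictor role less well.
3. Report beside it the between-arm difference in momentary affect during training, adjusted for ESM-baseline affect. This does not depend on how stressors are reported.
4. Report item 6 by arm. The mindfulness grounding exercises may change how often unpleasant thoughts are noticed, and a shift in the stressor slope should be read with that in mind.

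**Cost.** Some extra analysis and a few sentences of text, with no new data: items 1 and 6 are shown at every beep, including the ESM baseline. The baseline slope rests on at most 4×5 = 20 beeps per person, so the interaction will be less precise than a comparison within the training period. The simulations above did not test this phase contrast.

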##### Additional self-rated assessments

Participants will complete several additional self-rated assessments for the purpose of exploratory analysis. Participants will also complete a brief end of day questionnaire that will include a measure of mood, assessing presence and duration of different mood states. Nine moods will be investigated—happy, lively, content, satisfied, depressed, bored, anxious, irritable and tense. These items will allow for exploratory analysis of how individuals’ moods may relate to the two experimental conditions. The end of day questionnaire will also include items investigating whether participants have completed any exercises from their programme (decentering or control), how difficult these exercises were to complete, and whether these skills were relevant to their everyday life. This section is included both as a measure of adherence to the programme, and as a broad measure of participant feedback.

Our team is currently developing an adolescent friendly self-rated decentering inventory. A provisional version of this scale will be included at pre and post intervention as part of its on-going validation. We are also investigating the relationship between decentering and other emotion regulation skills. We will therefore include: the Cognitive Emotion Regulation Questionnaire,^44^ which is a 36-item questionnaire cataloguing a range of emotion regulation strategies (Cronbach’s α=0.62–.85); the Difficulties in Emotion Regulation Scale,^45^ which is a 36-item questionnaire investigating problems with emotion regulation (Cronbach’s α=0.94), including six subscales: non-acceptance of emotional responses; difficulty in engaging in goal-directed behaviour; impulse control difficulties; lack of emotional awareness; limited access to emotion regulation strategies; and lack of emotional clarity: and the Child and Adolescent Mindfulness Measure,^46^ which is a 10-item measure exploring trait mindfulness in children and adolescents (Cronbach’s α=0.88). Participants will complete the Coronavirus Anxiety Scale^47^ scales at baseline and post-intervention. This may help us address any unexpected impact of the COVID-19 pandemic on the intervention.

#### Far transfer effects

This study will include performance-based tasks to explore potential far-transfer effects of decentering training on cognition (research question 3). These include (1) affective cognitive control and (2) self-perspective processing, both of which have been posited as theoretical components of decentering.^6 29^ These measures will be administered at baseline and post intervention.

##### Affective cognitive control

This study will explore if decentering training influences the ability to maintain cognitive performance within emotional contexts (ie, affective cognitive control). This can be estimated via the Emotional Stop Signal Task (online supplemental figure S1).^48^ On each trial, a neutral or negative valence image is presented before a ‘go-signal’ that requires a speeded button-press (75% of trials). Participants must quickly make the appropriate button-press unless the go-signal is followed by a ‘stop-signal’ (25%). Participants must withhold their response on these trials. The period between the go and stop-signal (stop signal delay; SSD) varies over the task. Following a successful stop trial, the task is made more difficult by increasing the SSD by 25 ms. Following an unsuccessful stop trial, the task is made easier by decreasing the SSD by 25 m. This tracking algorithm typically causes a failure to stop on ~50% of trials. Sustained attention in emotional and non-emotional contexts will be estimated by calculating (1) the reaction time (RT) mean on go-trials and (2) the intertrial variability coefficient (ie, the RT mean divided by the RT SD). Inhibitory control in emotional and non-emotional contexts will estimated by calculating the *stop signal reaction time (*ie, mean RT−mean SSD).

10.1136/bmjopen-2021-056864.supp2Supplementary data

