##### Blinding

Research coordinators ([name] and [name]) will be blinded during assessment, data preprocessing and statistical analysis. Due to the nature of the study, it is not possible to remain blinded during participant allocation. This is because each participant needs to be given a secure link to the online training programme, either decentering training or the active control. All outcome assessments will be completed online; participants will access the same link to complete online assessments, regardless of group. Thus, there are no in-person data collectors with an awareness of participants’ allocation. Initial data will be preprocessed (eg, calculation of summary scores like means, percentage accuracy, sums, etc). Preprocessing will be completed using pre-existing scripts coded in R and MATLAB ([name]). At this point, the dataset will be shared with the trial statistician (PW) who will conduct the statistical analysis and who will be blind to participant allocation. Once the analysis is complete, the trial coordinators will unblind the dataset by indicating which participants were allocated to which group.

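### The reaction-time variability coefficient is defined upside down (mean/SD), and the protocol does not say whether stop-signal delay is tracked separately by image valence, on which the stop-signal reaction time contrast depends

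*Protocol article*

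**What the plan says.** All the definitions are in the protocol article, under Affective cognitive control (within Far transfer effects).

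- **Sustained attention.** "Sustained attention in emotional and non-emotional contexts will be estimated by calculating" two scores: the mean go-trial reaction time (RT), and "the intertrial variability coefficient (ie, the RT mean divided by the RT SD").
- **Inhibitory control.** "Inhibitory control in emotional and non-emotional contexts will estimated by calculating the" SSRT, given as "ie, mean RT−mean SSD".
- **Valence.** It varies from trial to trial: "On each trial, a neutral or negative valence image is presented before a" go-signal.
- **Tracking.** "Following a successful stop trial, the task is made more difficult by increasing the SSD by 25 ms", with an equal step down after a failed stop. The section gives a stop-failure rate of about 50% for the algorithm, not split by valence. It does not say whether neutral and negative trials have their own staircases.

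Under Blinding, the article adds: "Preprocessing will be completed using pre-existing scripts coded in R and MATLAB". The summary scores then go to the trial statistician. The Statistical analysis section covers performance-based measures in its heading and plans analysis of covariance adjusted for baseline.

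**The concern.** A score called a variability coefficient should rise with variability. This one falls. A statistician who receives a column labelled as variability, already computed by a script, could take a higher value to mean less stable attention when it means the opposite. Changing the sign afterwards is not a complete repair, because a reciprocal is not linear. It stretches differences among the steadiest responders and compresses those among the most erratic, which changes what a baseline-adjusted mean difference measures.

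For SSRT, subtracting mean delay from mean go RT relies on stopping failing on about half of the trials in each condition for which it is computed. The article states about 50% for the task as a whole but wants SSRT by emotional context. An overall 50% does not guarantee 50% within each context if one staircase runs across both. A real context effect on stopping could then be lost, or a mere slowing of go responses could pass for one.

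**Working it through.** **1. The coefficient.** The formula is from the protocol; the RT values are illustrative assumptions.

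| RT mean (ms) | RT SD (ms) | Protocol: mean/SD | SD/mean |
|---|---|---|---|
| 500 | 75 | 500/75 = 6.67 | 75/500 = 0.15 |
| 500 | 100 | 500/100 = 5.00 | 100/500 = 0.20 |
| 500 | 125 | 500/125 = 4.00 | 125/500 = 0.25 |
| 500 | 150 | 500/150 = 3.33 | 150/500 = 0.30 |

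The two columns move in opposite directions whatever RT values are chosen. On non-linearity: equal steps in SD/mean of 0.10, 0.15 and 0.20 become 1/0.10 = 10.0, 1/0.15 = 6.67 and 1/0.20 = 5.0, that is, gaps of 3.33 and then 1.67.

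**2. SSRT, algebra.** With the protocol's formula applied by valence,

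SSRT(neg) − SSRT(neu) = [RT(neg) − RT(neu)] − [SSD(neg) − SSD(neu)].

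If one staircase serves both valences in random order, mean SSD is the same in both up to chance. The second bracket is then about zero and only the go-RT difference remains.

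**3. SSRT, simulation.** Inputs from the protocol: 25% stop trials, 25 ms steps up and down, neutral or negative image on each trial. Assumptions not in the protocol: independent race between going and stopping; ex-Gaussian go RT (450, 50, 80 ms) in both contexts; true SSRT 220 ms neutral and 250 ms negative with a trial-to-trial SD of 20 ms; starting delay 250 ms; half of the trials per valence; 256, 400 or 2000 trials.

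The protocol's own figure first: at 400 trials with a shared staircase the failure rate is (42.8% + 55.9%)/2 = 49%, and with separate staircases (48.1% + 49.3%)/2 = 49%. The stated rate of about 50% is reproduced under either design, so it cannot tell them apart.

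Recovered difference, negative minus neutral (truth 30 ms):

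| Trials | Staircase | Failure rate neu / neg | Mean RT − mean SSD | Integration |
|---|---|---|---|---|
| 256 | shared | 42% / 56% | −0.7 ms | 26.0 ms |
| 400 | shared | 43% / 56% | −0.3 ms | 26.1 ms |
| 2000 | shared | 43% / 57% | 0.0 ms | 27.0 ms |
| 256 | separate | 47% / 49% | 26.1 ms | 29.5 ms |
| 400 | separate | 48% / 49% | 28.2 ms | 30.4 ms |
| 2000 | separate | 50% / 50% | 30.3 ms | 31.1 ms |

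The integration method takes the go-RT quantile at the observed P(respond|stop) in that context and subtracts mean SSD.

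Reverse case, 400 trials: no true SSRT difference, and negative images slow go RT by 30 ms. With a shared staircase the protocol's formula shows a spurious 30.0 ms (integration 3.7 ms). With separate staircases it shows 3.7 ms (integration 1.7 ms).

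**4. The between-group contrast.** Same assumptions, 400 trials. Suppose that training removes the 30 ms slowing in the negative context, so that true SSRT is 220 ms in both contexts for the trained group. With a shared staircase the protocol's score gives a group difference of about 14 to 15 ms in each context. With separate staircases it gives about 27 ms in the negative context and 1 to 2 ms in the neutral one.

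**The case against.** On the coefficient, it can be said that the formula is printed, that the score is introduced as an estimate of sustained attention (for which a higher mean/SD does mean steadier responding), and that this section states no directional hypothesis for it. The scoring scripts are not shown and may already use SD/mean. All of this stands. It makes misreading possible, not certain, and leaves open whether the fault is in the text or in the code. It does not remove the contradiction between the name and the formula.

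On SSRT, the objection is stronger. Mean RT minus mean SSD is a recognised estimator under tracking that holds failures near 50%, which is what the article describes. A reader might infer that SSRT is wrongly defined and that an effect of emotional context on stopping would go unseen. The document does not support that. It nowhere says that one staircase is shared; it gives a step rule and refers to a cited task and a supplementary figure, neither of which is at hand. With separate staircases the mean method recovers 26 to 30 ms of a true 30 ms, and the integration method adds little. Research question 3 also concerns training, a comparison between groups. Even with a shared staircase, the group difference in the example is diluted and spread over both contexts, but it is not lost altogether.

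**Conclusion.** The inverted coefficient is an error on the face of the text and rests on no assumption. Its consequence, reading a training effect on RT variability in the wrong direction, is a risk and not a certainty.

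The SSRT point holds only conditionally. If delay is tracked and averaged per valence, the protocol's formula is acceptable. If one staircase is shared, failure rates move to about 43% and 56% within contexts, and the contrast between contexts becomes the go-RT difference: about 0 ms for a true 30 ms, or 30 ms for a true zero. The sizes rest on the assumed RT distribution, SSRT values and trial counts. The loss of the contrast under a shared staircase follows from the algebra and held at all three trial counts.

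Both points are confined to the exploratory far-transfer outcomes. The Experiences Questionnaire, the experience-sampling and mental health outcomes, the mean go RT and the sample size are untouched. Severity is minor.

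**What to change.** 1. Define the intertrial variability coefficient as RT SD divided by RT mean, state that higher values mean less stable responding, and check that the preprocessing script computes the same. If the script already does so, only the text needs correcting.
2. State whether SSD is tracked, and mean SSD computed, separately for neutral and negative images. If so, the SSRT formula can stay.
3. If the staircase is shared, compute SSRT per valence by the integration method with the context-specific P(respond|stop).

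The cost is a sentence or two of text and a few lines of scoring code; data collection does not change. The integration estimate is somewhat noisier when stop trials are few. With a shared staircase, the simulated SD of one participant's context contrast was about 28 ms at 256 trials and 23 ms at 400. The mean method's SD was smaller there (16 and 14 ms), but around a value that carries no information on the SSRT contrast. With separate staircases the two methods were close (24.8 against 23.6 ms at 400 trials).
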